#### Laboratory Exclusions:

22.Any of the following liver function test criteria above specified limits: Total bilirubin >2.5 upper limit of normal (ULN); aspartate or alanine aminotransferase (AST/SGOT or ALT/SGPT) >2.5 ULN; alkaline phosphatase >2.5 ULN

#### Concomitant Therapy Exclusions:

23.Severe liver failure.24.Prior use of pirfenidone.25.Hypersensitivity/allergy against pirfenidone or any component of the investigational medicinal product (IMP).26.History of angioedema in relation to prior use of pirfenidone.27.Severe renal failure defined as GFR < 30 ml/min and/or need for dialysis.28.Concomitant therapy with potential interaction to study drug according to SmPC.29.Patients are excluded if more than 15 mg prednisolon equivalent are applied per day or if a pre-existent steroid and/or immunosuppressant therapy has been modified within the last 3 months and/or if such therapy would be needed to be changed during the study period. In that case, dosing has to be adjusted and patient must be re-checked for eligibility 3 months after the last dose adjustment.

### Concomitant therapy

Drugs that are considered necessary for the patient’s welfare may be given at the discretion of the investigator with respect to the potential interactions according to Summary of Product Characteristics (SMPC). However, careful monitoring for new symptoms by the patient is vital in this instance. Information on concomitant medications will be collected until the final Follow-Up Visit. For patients who withdraw from study, data on concomitant medications will be collected until the later of the following two time points:Time of consent withdrawal.28 days after last dose of study treatment.

With the exception of clinical deterioration (for definition see study endpoints) due to disease.

progression therapies listed below are not permitted during the study:

- Any investigational therapies (i.e., agents that are not approved by local regulatory agencies, including N-acetyl-cysteine (NAC) at a dose >600 mg/d)

- Any interferon therapy, including IFN-γ 1b

- Any cytokine modulators (including but not limited to etanercept and infliximab)

- Any other therapy that has been investigated or used off-label as a treatment for lung fibrosis including but not limited to d-penicillamine, colchicine, bosentan, imatinib mesylate, and cyclosporine A, rituximab. If patients receive any of these excluded therapies while on study, it will be recorded in the e-CRF and will be considered as a protocol violation.

In case of a clinical deterioration due to disease progression, pulse-dose steroids may be used for a period of up to 14 days, as well as any of the above mentioned and other “rescue” therapies such as plasma separation. This will be entirely left to the discretion of the investigator and have to be documented in the e-CRF.

## Statistical considerations

### Hypotheses

Hierarchical testing will be applied in the final analysis to test the treatment effect in different groups with regard to diagnosis (see Table 1 for diagnostic categories). The hypothesis H_0_: “no difference in absolute change in percent predicted FVC from baseline to week 48 between the pirfenidone and placebo group” will be tested against the alternative H_1_: “difference in absolute change in percent predicted FVC from baseline to week 48 between the pirfenidone and placebo group”. The order of hypothesis testing is defined as follows:H_0_ against H_1_ in the overall groupH_0_ against H_1_ in the group in which the diagnosis group with the smallest number of patients is excludedH_0_ against H_1_ in the group in which the diagnosis group with the second smallest number of patients is excludedH_0_ against H_1_ in the diagnosis group which has the highest number of patientsH_0_ against H_1_ in the diagnosis group which has the second highest number of patientsH_0_ against H_1_ in the diagnosis group which has the third highest number of patientsH_0_ against H_1_ in the diagnosis group which has the smallest number of patients

Hypotheses are tested consecutively until the *p*-value of a hypothesis exceeds the 5% significance level, thereby controlling the familywise error rate (FWER) at the 5% level.

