### Sample size

The sample size and power calculations are based on the analysis of the primary efficacy endpoint in the overall group: absolute change in percent predicted FVC from baseline to week 48. It is assumed that the primary efficacy endpoint is not normally distributed and that its probability distributions are identical in both treatment populations, except for location. Assuming furthermore a similar treatment effect in all clinical diagnosis groups (see Table 1 for diagnostic categories), the two-sample Mann-Whitney U Test for independent samples is used to test for a difference in median. For a group sequential design according to O’Brien/Fleming with one interim analysis, a two-sided significance level of 5% and a power of 80%, 187 patients per arm are needed to detect an effect size of 0.3 between the two treatment groups across all indications. The magnitude of the effect size was based on the observed rank effects (i.e. effect in a non-parametric analysis) of pirfenidone versus placebo in the CAPACITY study at 1 year (48 weeks) corresponding to an effect size of 30% after scaling back. In the pooled CAPACITY studies the effect size was around 40%. The conservative choice of the effect size allows for a dropout rate like in CAPACITY [1].

Sample size calculation in ADDPLAN 6.0 is only available for group sequential designs based on t tests. Therefore, the results were multiplied by the factor π/3 for nonparametric adjustment as proposed by Al-Sunduqchi and Guenther (1990) (Determining the Appropriate Sample Size for Inferences Based on the Wilcoxon Statistics. Ph.D. dissertation under the direction of William C. Guenther, Dept. of Statistics, University of Wyoming, Laramie, Wyoming) and implemented in PASS 2008 [22].

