### Interim analysis

There is one planned interim analysis for efficacy. An interim analysis will be performed after completion of treatment in 224 patients which is expected to occur at about two and a half years after start of accrual. The significance level in the interim analysis is 0.0101 and the power for a positive result in the interim analysis is about 35% if the true effect size equals 0.3.

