### Primary endpoint

The primary efficacy analysis will be to investigate the treatment effect on the absolute change in percent predicted FVC from baseline in the pirfenidone and placebo group with regard to each hypothesis tested. As the primary efficacy endpoint is assumed to be not normally distributed, data will be analyzed using a rank analysis of covariance (ANCOVA) model with a classification effect for treatment and diagnostic category and baseline FVC as a covariate. The null hypothesis is tested against the alternative hypothesis at a two-sided significance level of 5%. The treatment effect will be tested using the Cochran-Mantel-Haenszel mean score statistic, median treatment differences will be estimated according to Hodges-Lehmann. The applied methods are based on a location-shift model assuming that the metric distributions of the absolute change in percent predicted FVC are the same, except for location. Furthermore, the primary efficacy endpoint will be analyzed by factorial ANCOVA with a classification effect for treatment and diagnostic category (with and without an interaction term for treatment and diagnostic category) and baseline FVC as a covariate.

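### The final test of the overall group is set at the full 5% after an efficacy interim at 0.0101, so the claimed 5% familywise error rate does not hold

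*Protocol article*

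**What the plan says.** Four sections of the protocol article bear on the level of the primary test.

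- **Sample size:** the calculation is made "For a group sequential design according to O’Brien/Fleming with one interim analysis", two-sided 5% and 80% power, giving 187 patients per arm for an effect size of 0.3. The 5% here is the overall level of the two-stage design.
- **Interim analysis:** "There is one planned interim analysis for efficacy". Its timing is fixed: "An interim analysis will be performed after completion of treatment in 224 patients". So is its level: "The significance level in the interim analysis is 0.0101". The chance of a positive interim result is put at about 35%.
- **Hypotheses:** for the final analysis, seven hypotheses are tested in a fixed order, beginning with the overall group. Testing continues until a p-value "exceeds the 5% significance level, thereby controlling the familywise error rate (FWER) at the 5% level".
- **Primary endpoint:** "The null hypothesis is tested against the alternative hypothesis at a two-sided significance level of 5" per cent.

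No section gives a reduced level for the final stage.

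**The concern.** The interim and step 1 of the final hierarchy test the same null hypothesis: no treatment difference in change in percent predicted FVC in the overall group. The interim is an efficacy look with its own rejection level, so part of the 5% is spent there. Testing again at the full 5% gives two chances to reject, and their combined probability under the null exceeds 5%.

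The overall-group test decides the primary endpoint and is the gate to six further tests in diagnosis-defined groups. If the final p-value fell between 0.0464 and 0.05, the Hypotheses section would declare success and open the subgroup tests, while the design under Sample size and Interim analysis would not reject. Settling that after unblinding would be a choice made with the result in view.

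**Working it through.** **Inputs (all from the protocol article)**

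| Input | Value | Section |
|---|---|---|
| Overall two-sided level, power | 5%, 80% | Sample size |
| Boundary | O'Brien/Fleming, one interim | Sample size |
| Patients | 187 per arm, 374 in total | Sample size |
| Effect size; nonparametric factor | 0.3; π/3 | Sample size |
| Interim timing, level, power | 224 patients, 0.0101, about 35% | Interim analysis |
| Threshold in the final analysis | 5% | Hypotheses |

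Assumption: information is proportional to the number of patients completing treatment. The information fraction is then t = 224/374 = 0.599. The interim and final statistics Z1 and Z2 are jointly normal with correlation √t = 0.774.

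**Step 1. Reproduce the plan's design.** The classical O'Brien/Fleming boundary rejects if |Z1| > c/√t or |Z2| > c. Solving P(|Z1| > c/√t or |Z2| > c) = 0.05 under the null by numerical integration gives c = 1.992.

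- Interim: 1.992/0.774 = 2.574, a two-sided level of 0.0101. This matches the stated figure.
- Final: 1.992, a two-sided level of 0.0464.
- The O'Brien-Fleming-type spending function would give 0.0113 at the interim, which does not match. The classical boundary is therefore the one used.

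**Step 2. Check the sample size and interim power under that boundary.** For 80% power the required drift at full information is θ = 2.820.

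- Per arm: 2 × (2.820/0.3)² = 176.7 by normal approximation.
- The usual t-test correction adds c²/4 = 1.992²/4 = 0.99, giving 177.7, rounded up to 178.
- 178 × π/3 = 186.4, rounded up to 187. This matches.
- With 187 per arm, the t-test equivalent is 187 × 3/π = 178.6 and θ = 0.3 × √(178.6/2) = 2.835. Interim power is P(Z1 > 2.572) = 35.3%, against about 35% stated.

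The stated interim level, sample size and interim power all agree with a design whose final level is 0.0464.

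**Step 3. Apply the rule as written.** Reject if p < 0.0101 at the interim (|Z1| > 2.572) or p < 0.05 at the final analysis (|Z2| > 1.960):

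P(|Z1| > 2.572 or |Z2| > 1.960) = 0.0535.

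Of this, 0.0101 arises at the interim and 0.0535 − 0.0101 = 0.0434 at the final analysis. The plain sum 0.0101 + 0.05 = 0.0601 overstates the error, because the two statistics are correlated. Keeping 0.0101 fixed and moving the interim, the error is 0.0546 at t = 0.50 and 0.0523 at t = 0.70, so it exceeds 0.05 throughout that range.

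**Step 4. Apply the correct final level.** With 0.0101 spent at t = 0.599, the final critical value that holds 5% overall is 1.992, a level of 0.0464. Power at 187 per arm is then 80.4%, against 81.2% with a final test at 5%. The planned 80% is met either way.

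**The case against.** The strongest counter-argument is that 5% means the overall level throughout. The Sample size section uses it that way for the group sequential design, and the Primary endpoint section uses nearly the same phrase without calling it a final-stage cut-off. On this view the Hypotheses sentence deals only with multiplicity across the seven ordered hypotheses, the O'Brien/Fleming design deals with the interim, and the final boundary is a detail that an article may leave to the full protocol or SAP. The trial is also an exploratory phase II study, and the inflation is slight.

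Part of this stands. The Primary endpoint sentence alone can be read as the overall level. The design itself was built correctly, and the excess is small.

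The reading fails for the Hypotheses section. That section governs the final analysis, compares each p-value directly with 5%, and says that this controls the familywise error rate. It does not say that the p-value is adjusted for the sequential design. The fault is a stated decision rule with a wrong claim attached, so it is more than a missing detail. An SAP that used 0.0464 would contradict it. Having set itself a formal efficacy boundary and a familywise guarantee, the trial should meet them, exploratory or not.

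**Conclusion.** The concern holds: the rule is wrong as written. Under it the two-sided type I error for the overall-group hypothesis is 5.35%, where 5% is claimed. The final level consistent with the plan's own design is 0.0464. The practical consequence is confined to a final p-value between 0.0464 and 0.05, but there it decides both the primary result and whether the subgroup tests open.

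The result assumes that information is proportional to completed patients, that the interim takes place at 224 of 374, and that crossing 0.0101 there counts as rejection, as the stated power for a positive interim result implies. The false claim concerns step 1. Steps 2 to 7 are planned for the final analysis only, so each is tested once and the interim adds no second look at them. That would change if the hierarchy were also run after an interim rejection, a case the article does not address.

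**What to change.** In the Hypotheses and Primary endpoint sections, replace the 5% threshold for the overall group in the final analysis with the O'Brien/Fleming final level: two-sided 0.0464 (|Z| > 1.992) at the planned timing, recomputed from the information fraction actually reached at the interim. Keep 5% only as the overall level of the two-stage design.

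State that steps 2 to 7 open only if the overall group crosses its group sequential boundary. In the same place, state the level at which those steps are tested and what happens to the hierarchy if the overall group crosses at the interim.

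The cost is a sentence or two in the protocol and SAP and a slightly stricter final threshold. The sample size stays at 187 per arm, with 80.4% power. The change should be made before the interim analysis.

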### Analysis population

The intention-to-treat (ITT) population is defined as all randomized patients. All analyses of outcome parameters will be based on the intention-to-treat population.

The per protocol (PP) population comprises all patients who had no major protocol deviation with respect to the primary endpoint. The analysis of the primary endpoint will also be provided for the per protocol population.

The as treated population is defined as all included patients who received at least one dose of the investigational medicinal product (IMP). Analysis of safety will be based on the as treated population, i. e. patients will be analyzed according to the treatment they actually received.

### Sample size

The sample size and power calculations are based on the analysis of the primary efficacy endpoint in the overall group: absolute change in percent predicted FVC from baseline to week 48. It is assumed that the primary efficacy endpoint is not normally distributed and that its probability distributions are identical in both treatment populations, except for location. Assuming furthermore a similar treatment effect in all clinical diagnosis groups (see Table 1 for diagnostic categories), the two-sample Mann-Whitney U Test for independent samples is used to test for a difference in median. For a group sequential design according to O’Brien/Fleming with one interim analysis, a two-sided significance level of 5% and a power of 80%, 187 patients per arm are needed to detect an effect size of 0.3 between the two treatment groups across all indications. The magnitude of the effect size was based on the observed rank effects (i.e. effect in a non-parametric analysis) of pirfenidone versus placebo in the CAPACITY study at 1 year (48 weeks) corresponding to an effect size of 30% after scaling back. In the pooled CAPACITY studies the effect size was around 40%. The conservative choice of the effect size allows for a dropout rate like in CAPACITY [1].

Sample size calculation in ADDPLAN 6.0 is only available for group sequential designs based on t tests. Therefore, the results were multiplied by the factor π/3 for nonparametric adjustment as proposed by Al-Sunduqchi and Guenther (1990) (Determining the Appropriate Sample Size for Inferences Based on the Wilcoxon Statistics. Ph.D. dissertation under the direction of William C. Guenther, Dept. of Statistics, University of Wyoming, Laramie, Wyoming) and implemented in PASS 2008 [22].

### Interim analysis

There is one planned interim analysis for efficacy. An interim analysis will be performed after completion of treatment in 224 patients which is expected to occur at about two and a half years after start of accrual. The significance level in the interim analysis is 0.0101 and the power for a positive result in the interim analysis is about 35% if the true effect size equals 0.3.

### Primary endpoint

The primary efficacy analysis will be to investigate the treatment effect on the absolute change in percent predicted FVC from baseline in the pirfenidone and placebo group with regard to each hypothesis tested. As the primary efficacy endpoint is assumed to be not normally distributed, data will be analyzed using a rank analysis of covariance (ANCOVA) model with a classification effect for treatment and diagnostic category and baseline FVC as a covariate. The null hypothesis is tested against the alternative hypothesis at a two-sided significance level of 5%. The treatment effect will be tested using the Cochran-Mantel-Haenszel mean score statistic, median treatment differences will be estimated according to Hodges-Lehmann. The applied methods are based on a location-shift model assuming that the metric distributions of the absolute change in percent predicted FVC are the same, except for location. Furthermore, the primary efficacy endpoint will be analyzed by factorial ANCOVA with a classification effect for treatment and diagnostic category (with and without an interaction term for treatment and diagnostic category) and baseline FVC as a covariate.

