**Discussion:**

There is an urgent unmet clinical need for effective therapies for patients with a progressive fibrotic lung disease other than IPF. The current study protocol is unique with respect to selecting patients with different disease entities of lung fibrosis which have, however, essential pathophysiological characteristics in common. Moreover, by selecting patients with evidence of disease progression despite conventional therapy, the protocol ensures that a cohort of interstitial lung disease (ILD) patients with a high unmet medical need is targeted and it may allow a sufficiently high event rate for evaluation of treatment responses.

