## Methods/Design

RELIEF is a prospective, randomized (1:1), placebo-controlled clinical trial enrolling patients with progressive fibrotic lung disease due to CVD-LF, fNSIP, cHP or ALF, despite conventional anti-inflammatory therapy. The progressive character of the underlying fibrotic lung disease has to be objectively documented by at least three pulmonary function tests within 6 to 24 months prior to enrollment demonstrating an annualized percent predicted FVC decline of ≥5% (absolute). The change in lung function is determined by employing the DZL-FVC slope calculator, a tool available on the German Center for Lung Research DZL website (http://www.dzl.de/index.php/de/forschung/tools/fvc-slope-calculator).

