### Study population

Symptomatic patients at the age of 18–80 years with a confident diagnosis (at least 9 months before randomization) of progressive, non-IPF lung fibrosis due to ALF, CVD-LF, cHP or fNSIP according to the diagnostic criteria outlined in Table 1 are eligible for this study. In addition, disease progression despite previous or concomitant treatment (CVD-LF, chronic HP, fNSIP) or without specific therapy (ALF) must be documented by calculating the slope of a set of at least three previous FVC measurements within at least six to a maximum of 24 months before screening, showing an (eventually extrapolated) FVC decline of at least 5 % (abs. Pred.) per year.

**Table 1 Tab1:** Diagnostic Criteria of RELIEF Patient Categories (all to be fulfilled within each category)

Lung fibrosis associated with collagen / vascular diseases
• Diagnosis of progressive systemic sclerosis (PSS), rheumatoid arthritis (RA), Sjörgen’s syndrome, polymyositis/dermatomyositis on the basis of extrapulmonary symptoms and corresponding proof of auto-antibodies
• Reticular changes in HRCT and restrictive lung function pattern
• Absence of an alternative explanation for fibrotic lung disease
Fibrotic NSIP
• Histological diagnosis of a fibrotic NSIP pattern by open lung biopsy or cryobiopsy
• HRCT consistent with fibrotic NSIP
• Restrictive lung function pattern
• Absence of an alternative explanation for fibrotic lung disease, especially no clinical suspicion of CVD
Chronic Hypersensitivity Pneumonitis
• Previous or current respiratory symptoms (dyspnea, coughing) with a temporal or spatial relation to a causative antigen exposure
• Proof of precipitating antibody and/or lymphocytic alveolitis (>30%)
• HRCT consistent with chronic HP
• Restrictive lung function pattern
• Absence of an alternative explanation for fibrotic lung disease
Asbestos-induced lung fibrosis
• Existence of asbestos-specific pleural changes in HRCT (pleural plaques)
• Reticular changes in HRCT and restrictive lung function pattern
• History of asbestos exposure
• Absence of an alternative explanation for fibrotic lung disease
• Absence of extensive pleural plaques and/or effusion

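### Optional gain in precision: the primary and supporting FVC models could also adjust for the pre-randomisation FVC slope that eligibility already requires

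*Protocol article*

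**What the plan says.** **Model.** In the protocol article, the Primary endpoint section prescribes a rank ANCOVA with a "classification effect for treatment and diagnostic category and baseline FVC as a covariate". It adds a factorial ANCOVA, run with and without a treatment-by-diagnosis interaction, on the same covariates. Prior rate of decline is in neither model.

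**Eligibility.** The Study population section requires progression to be shown by "calculating the slope of a set of at least three previous FVC measurements", taken over 6 to 24 months, with a decline of at least 5 points of percent predicted FVC per year. Methods/Design names the tool: "The change in lung function is determined by employing the DZL-FVC slope calculator".

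**Purpose of the selection.** The Discussion part of the abstract says that, "by selecting patients with evidence of disease progression despite conventional therapy", the trial targets a group with high unmet need, and that "it may allow a sufficiently high event rate for evaluation of treatment responses". The slope has no other stated use.

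**The concern.** The primary endpoint is a 48-week change in percent predicted FVC. The eligibility slope is an annual change on the same scale, measured before randomisation. Baseline FVC carries the level of lung function but not its rate of change. The entry threshold has no upper limit on the rate of decline, so rates can still differ among enrolled patients, yet the plan uses the slope only as a yes/no entry criterion.

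If the remaining variation in slope predicts the 48-week change, adjusting for it would reduce residual variance and raise power without more patients. That potential precision is all that is at stake. The validity of the comparison is not.

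**Working it through.** **Inputs from the article**
- Sample size section: effect size 0.3, two-sided 5%, power 80%, O'Brien/Fleming design with one interim analysis, factor π/3, 187 per arm.
- Interim analysis section: interim after 224 patients, level 0.0101, interim power about 35%.
- Information fraction at the interim: 224/374 = 0.599.

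**Step 1: reproduce the plan's own figures, without any slope term**
- Fixed-sample t test at effect size 0.3: 175.4 per arm.
- O'Brien/Fleming inflation at 0.599: 1.0133, so 175.4 × 1.0133 = 177.7.
- Times π/3: 186.1, rounded up to 187. This matches.
- Interim critical value 2.574, two-sided level 0.0101. This matches.
- Interim power with 112 per arm: 35.3%. This matches.
- Overall power with 187 per arm, normal approximation: 80.4%. The drift is 0.3 × √(187/2 × 3/π) = 2.835.

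The design calculation rests on a two-sample Mann-Whitney test, so it does not count on the slope.

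**Step 2: add the slope**

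Let ρ be the partial correlation of the prior slope with the 48-week change, given baseline FVC and diagnosis. The article gives no value, so ρ is assumed. The planning effect size of 0.3 is taken to apply to the model as it stands. Residual variance is then multiplied by 1 − ρ² and the drift becomes 2.835/√(1 − ρ²). The sample size giving the same precision as 187 per arm without the slope is 187 × (1 − ρ²).

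| Assumed ρ | 1 − ρ² | Power at 187 per arm | Equivalent n per arm |
|---|---|---|---|
| 0 | 1.00 | 80.4% | 187 |
| 0.1 | 0.99 | 80.8% | 186 |
| 0.2 | 0.96 | 82.0% | 180 |
| 0.3 | 0.91 | 84.0% | 171 |
| 0.4 | 0.84 | 86.7% | 158 |

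**Step 3: which values of ρ are plausible**

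Two features of the design pull ρ down.

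*Noise.* For three equally spaced values over T years with within-patient SD s, the standard error of the slope is s√2/T. With an assumed s of 3 points, this is 3 × 1.414/0.5 = 8.5 points per year over 6 months and 3 × 1.414/2 = 2.1 over 24 months. Over a short window the error can exceed the 5-point threshold itself.

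*Truncation.* Only patients with an estimated decline of at least 5 points per year enter. An illustrative simulation assumed a mean true slope of −3 or −5 points per year, a true-slope SD of 4 to 6, a slope standard error of 2 to 6 and a residual SD of 7. The correlation of slope with later change was 0.26 to 0.59 before selection and 0.15 to 0.40 after it. These are simple correlations. The simulation includes neither baseline FVC nor diagnosis, so it guides ρ only roughly. At 0.15 the power lies between the table's 80.8% and 82.0%, a gain of about one point.

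**The case against.** The strongest objection is that nothing here is wrong. Treatment, diagnostic category and baseline FVC make a valid, conventional model. In a 1:1 randomised trial, leaving out a further baseline covariate does not bias the comparison or inflate the type I error. All of this stands, which is why the point is only an improvement.

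A reader might infer that the trial itself regards the slope as prognostic and then ignores it. The article does not support that. The abstract's Discussion ties progression to unmet need and event rate, and the section on idiopathic fibrotic NSIP calls progression after failed therapy prognostically relevant. Both concern progression as a status that the enrolled patients share. Nothing says that a steeper slope beyond the threshold predicts a larger 48-week loss.

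A reader might also infer that chance imbalance in slope threatens the single-diagnosis tests. Such imbalance is already covered by the error rate of those tests, and they are reached only after all three pooled hypotheses have been rejected.

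Two practical cautions stand. The intention-to-treat set is all randomised patients, so someone randomised in breach of the slope criterion could lack a valid value. The article also does not say that the slope is stored as trial data. In addition, slopes from 6-month and 24-month windows differ widely in precision, which limits the benefit.

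Finally, the analysis plan, which is not shown, may contain a slope-adjusted sensitivity analysis. That is possible, and its absence from the article is not criticised. The point concerns the covariates that the article does fix for the primary model and its factorial companion.

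**Conclusion.** The point holds as a low-cost improvement. Both stated models omit a baseline measure that eligibility requires, that is on the outcome's own scale and that the trial uses for enrichment. The omission contradicts nothing in the article and leaves the 187 per arm, the interim level and the interim power intact. It would be wrong to call it an error, a source of bias or a shortfall in power.

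The size of the benefit is uncertain. It is about 0.4 points of power at ρ = 0.1, 1.6 at 0.2, 3.6 at 0.3 and 6.3 at 0.4. These figures rest on an assumed partial correlation and on the planning effect size of 0.3. Truncation and noisy three-value slopes make the lower end plausible, so about one point is a realistic expectation.

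**What to change.** Before any unblinding, including for the interim efficacy analysis, pre-specify the ranked annualised FVC slope from the eligibility calculation as an additional covariate in both the rank ANCOVA and the factorial ANCOVA. Keep baseline FVC and diagnostic category, and use the same covariates at the interim and final analyses.

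State a simple, treatment-blind rule for any randomised patient without a valid slope, for example assigning the median rank, so that no one leaves the intention-to-treat set.

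The cost is a line or two in the analysis plan and a check that the slope, or the FVC values and dates behind it, is held in the trial database. The sample size need not change, and any gain is best treated as a margin.
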